## 4. Discussion

As far as the authors know, this study represents the first RCT focused on early powered mobility for young children with SMA1. The primary aim of this RCT is to evaluate the effectiveness of an early-powered mobility intervention, delivered in the child’s natural environment, for participation, functional ability, and quality of life for young children diagnosed with SMA1 with severe motor impairments. 

There is increasing evidence indicating that early powered mobility training can be highly beneficial for very young children who are unable to move independently and are unlikely to achieve independent mobility in the future [20,22,23,24,50]. In this context, incorporating self-initiated powered mobility through a MROC can play a pivotal role in a comprehensive intervention plan for children with SMA1. 

The MROCs employed in this RCT are electric toys specifically designed to promote self-initiated mobility, enabling children to actively participate in daily activities within their natural environments. By facilitating such mobility, MROCs can enhance children’s independence, autonomy, and self-confidence [25]. Compared to traditional powered wheelchairs, MROCs offer several distinct advantages. They are generally more cost-effective and easier to transport, making them more accessible to a broader range of families. Their toy-like appearance not only makes them more attractive to children but also allows for easier adaptation to the child’s evolving needs and family goals [23,24]. This adaptability is crucial for maintaining engagement and meeting the specific requirements of each child and their family. Despite these advantages, MROCs are not without limitations. They may struggle to navigate uneven terrain or steep slopes, which can restrict their utility in certain environments. Additionally, their design may limit their speed, making them less suitable for rapid outdoor travel. These limitations need to be considered when integrating MROCs into a child’s mobility plan, ensuring that they complement other interventions and address the child’s specific needs effectively. Overall, while MROCs offer a promising and accessible option for enhancing mobility and participation among young children with severe motor impairments, careful consideration of their limitations is essential for optimizing their effectiveness as part of a broader therapeutic strategy.

Evaluating the impact of interventions on participation is crucial, as participation enables children to interact with their peers, acquire knowledge, develop skills, and express creativity, all of which foster cognitive, perceptual, social, and motor development [40]. Participation-based interventions can also improve functional activity and bodily functions, as well as motivation to explore and engage with the environment [16,21]. Therefore, this study may make a significant contribution to evidence-based clinical practice by providing recommendations on the early use of low-cost powered mobility devices in natural settings for children with SMA1.

Family-centered interventions, where parents are actively involved in the training program, can improve the child’s functional performance and empower caregivers by deepening their understanding of their child’s needs. Involving families can also amplify the effects of interventions and assist children in applying learned skills to everyday tasks [51]. Therefore, this study will actively engage families in both the planning and implementation of the intervention, including the formulation of functional goals and the development of the intervention strategy. Families will play a critical role, and children will also be actively involved. During treatment sessions, family members and therapists will encourage children to explore their environment, promote independent mobility, and address mobility challenges encountered during daily activities and social interactions [50,51].

This study may face some limitations. Adherence to the intervention could be challenging due to the fragility and age of the participants. Families of children with SMA1 often have concerns about their children participating in outdoor activities or attending nursery schools. Additionally, the potential for medical complications associated with SMA1 could present challenges. Another potential limitation is the use of the ALP tool, which does not account for the child’s age. Consequently, younger children might not achieve higher levels in the ALP tool, potentially reflecting developmental constraints rather than limitations imposed by the disease.

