For young children with severe mobility limitations, such as those with SMA1, there can be considerable restrictions in participation and reduced social interaction with caregivers and peers. These limitations often result from the poor self-initiated mobility and delays in learning how to move and cognitive development [12,13]. Dunaway et al. [14] point out that there is a critical therapeutic window for mobility development, suggesting that strategies focused on self-initiated movement can profoundly impact behavior, self-esteem, and social participation. Ideally, providing independent mobility should occur around between 7 and 12 months, as close as possible to the typical ages for crawling and walking, to help minimize delays in cognitive development and facilitate more effective social and motor development [14]. Powered mobility devices offer a means for self-initiated movement and environmental exploration [15]. It is also associated with benefits that extend beyond mobility, potentially improving social skills [14,15,16], communication, cognitive development, and peer interactions [17,18].

Therefore, children with SMA1 are likely to benefit from the early introduction of powered mobility as a valuable strategy intervention for moving, playing, and engaging with their natural environment [17,19]. This approach represents a significant shift in how we support children with SMA, potentially expanding their world and fostering greater social interaction and independence [19,20,21].

A systematic review conducted by Hospodar et al. [20] evaluated the use of modified ride-on cars (MROCs) for children with mobility limitations. The review found that children as young as 7 months could engage with these toys, which enhanced their activity levels and participation. Additionally, MROCs positively impacted family-related outcomes. MROCs are engaging toys that can encourage interaction between infants with mobility limitations and their peers, thereby enhancing social participation [22,23,24]. Positive effects were observed in terms of enjoyment during powered mobility interventions and improved social skills, including better interaction with peers in playgrounds and in playgroups [17,18,20].

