### 2.1. Study Sample

Children with SMA1, between 10 months and 5 years old, who have no prior experience with powered mobility interventions or have used a powered mobility device for less than 7 h in the month preceding this study will be included. Exclusion criteria are children with severe visual impairments, a body weight exceeding 25 kg—MROC requirement, those who use a respirator, or those with other health conditions affecting the neuromusculoskeletal system that may interfere with the use of powered mobility [26,29].

Sample size calculation was performed using G*Power version 3.1.9.4. The calculation was based on the following parameters: an alpha (α) level of 0.05, which corresponds to a 5% chance of a type I error (incorrectly rejecting the null hypothesis when it is true); a statistical power (1-β) of 0.80, which means there is an 80% chance of correctly rejecting the null hypothesis if there is a true effect; and a medium effect size of 0.5 due to the lack of previous studies in this population and the use of powered mobility. Based on these parameters, the calculation determined that 26 participants, with 13 participants in each group, would be needed to achieve adequate statistical power for this study. To account for a potential dropout rate of 20%, a total of 32 participants will be recruited (*n* = 16 for each group) to ensure that the final sample size remains sufficient for analysis.

Recruitment will be performed at early care centers in collaboration with the Spanish Spinal Muscular Atrophy Foundation (*FUNDAME: Fundación de Atrofia Muscular Espinal*). An informational session will be held with the families of potential participants to explain the aims and procedures of this study.

Once families have shown their desire to participate and signed the informed consent forms, a member of the research team—not involved with assessments or interventions—will randomly assign the participants to two groups: the experimental group and the control group (waiting list group).

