Participation: measured with the Spanish version of the Young Children’s Participation and Environment Measure (YC-PEM) [30]. The YC-PEM provides insights into family members’ perspectives on the participation of children from 0 to 5 years old in various activities at home, preschool, and the community. For each activity type, the frequency of participation is rated on a scale from 0 to 7 (0 = never; 7 = one or more times a day). Participation level is rated on a 5-point scale (1 = little involvement; 5 = very involved), and desired changes in participation are recorded as yes or no. Additionally, the impact of environmental characteristics and resources on participation is rated on a scale from 1 to 3 (1 = usually difficult/usually not; 3 = generally helps/usually yes).Functional ability: assessed using the Pediatric Evaluation of Disability Inventory–Computer Adaptive Test (PEDI-CAT) questionnaire [31]. Parents or caregivers complete the PEDI-CAT through an adaptive computer platform. The PEDI-CAT includes a bank of items across two domains: Mobility (75 items, ranging from basic motor skills to more complex skills, including the use of walking devices) and Social/Cognitive (60 items covering interaction, communication, daily cognition, and self-control).Quality of life: evaluated using the Spanish version of the Pediatric Quality of Life Inventory (PedsQL)-Neuromuscular module [32]. The PedsQL is a parent-reported tool designed to evaluate perceptions of the child’s quality of life. It includes three dimensions: 17 questions on neuromuscular disease, 3 questions on communication, and 5 questions about family resources. Responses range from 0 (never) to 4 (almost always), which are converted into a score from 0 to 100. Scores are interpreted as follows: 100—never; 75—almost never; 50—sometimes; 25—frequently; and 0—almost always.*Secondary outcomes:*Learning of powered mobility: assessed with the Assessment of Learning Powered Mobility (ALP) [33]. The ALP describes 8 levels of performance (1 = beginner; 8 = expert) in using a powered mobility device, based on five categories: attention level; activity and movement; comprehension of the mobility device; expressions and emotions; and interaction and communication [34]. The ALP levels will be assessed weekly to help guide families on the strategies to use during their sessions and ensure consistent progress.Functional goals: measured with the goal attainment scale (GAS) [35] at baseline and at weeks 4, 8, 12, and 16 assessments. The goals focus on the use of powered mobility in the child’s natural environment and will be developed in collaboration with the child’s family and/or caregivers.Parental stress: assessed with the Spanish version of the Parenting Score Index-Short Form (PSI-SF) [36] at baseline and weeks 8, 12, and 16. The PSI-SF is a 36-item self-reported questionnaire that includes three subscales: parental distress (PD), parent–child dysfunctional interaction (PCDI), and difficult child (DC).Satisfaction with home intervention: scored with the Spanish version of the Client Satisfaction Questionnaire (CSQ-8) [37] at weeks 4, 8, and 12. The CSQ-8 measures overall satisfaction with the received service through 8 items scored on a scale from 1 to 4. The total score ranges from 8 to 32, with higher scores indicating greater satisfaction.Satisfaction with the use of the powered mobility device: assessed with the Spanish version of the Quebec User Evaluation of Satisfaction with assistive Technology Version 2.0 (QUEST 2.0) [38] at week 16 by the end of this study. The QUEST 2.0 is a self-administered instrument designed to assess satisfaction with various assistive technologies and related services. It comprises two subscales for devices and services. Each item is rated from 1 (not satisfied) to 5 (very satisfied). The device subscale contains 8 questions addressing the following dimensions: size, durability, weight, safety, fit, comfort, ease of use, and effectiveness. The services subscale contains 4 questions evaluating the provision of services, professional services, repairs, and follow-up support for the device.

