### 2.8. Statistical Analysis

Quantitative data will be analyzed using SPSS Statistics 22.00 for Windows. Parametric statistical tests will be employed with a significance level set at *p* < 0.05. To compare outcome variables between interventions, the paired Student’s *t*-test will be employed for comparisons involving two measures. For comparisons involving more than two measures, repeated measures ANOVA will be used to identify specific differences between groups or time points. To provide a comprehensive understanding of the results, effect sizes will be calculated for both the *t*-test and ANOVA. Confidence intervals for these effect sizes will also be reported to offer insights into the robustness of the findings.

Photovoice data will be transcribed by the researchers who conducted the online meetings with the families. The transcriptions will be reviewed by an experienced qualitative researcher [48]. Two researchers will independently analyze the data, followed by a group discussion with the research team to develop preliminary results. Thematic analysis will be performed following the principles outlined by Braun and Clarke [49] with support from ATLAS.ti software v.23. Identified themes will be validated by the participating families, who act as co-investigators in this study. This phase, termed “Validation of Analysis by Parents”, allows families to select the themes that best reflect the content of the sentences and photos included in the analysis.

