## 3. Results

This randomized controlled trial (RCT) aims to enhance understanding of the positive impacts of powered mobility on participation, functional ability, and quality of life in children with SMA1. It is anticipated that this intervention will lead to a significant improvement in these areas.

Specifically, it is expected that children will demonstrate an increase of at least 2 points in their ALP level during the structured program. Furthermore, ongoing progress is anticipated throughout the follow-up period, reflecting sustained benefits from the intervention.

Family involvement in the implementation of the intervention and the establishment of functional goals is crucial. Engaging families not only facilitates the practical application of the intervention but also provides valuable insights into the real needs and challenges faced by children with SMA1. This feedback will be instrumental in refining future research and therapeutic strategies.

By exploring these factors, this study aims to offer more precise guidance on optimizing therapeutic approaches for this vulnerable population. The results will provide a more comprehensive overview of the study’s goals and anticipated outcomes, emphasizing the importance of family involvement and the potential impact on future research and therapeutic strategies.

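### Age spans 10 months to 5 years and is named as a possible limit on ALP level, but the stated analysis has no age term and one ALP gain is expected at every age

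*Protocol article*

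**What the plan says.** - Section 2.1 admits children "between 10 months and 5 years old". It plans 13 evaluable children per group and mentions no stratification of the randomisation by age.
- Section 2.2 lists the ALP among the secondary outcomes: "The ALP describes 8 levels of performance". It is rated weekly to guide the sessions.
- Section 2.8 gives paired t-tests where there are two measures. Where there are more, "repeated measures ANOVA will be used to identify specific differences between groups or time points". It names no covariate and does not refer the reader elsewhere for covariates.
- Section 3 states that "it is expected that children will demonstrate an increase of at least 2 points in their ALP level during the structured program", without distinguishing ages.
- Section 4 (Discussion) lists as a limitation that the ALP makes no allowance for age, so that "younger children might not achieve higher levels in the ALP tool, potentially reflecting developmental constraints rather than limitations imposed by the disease".

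**The concern.** The article itself raises age as something that may shape one of its outcomes. It then describes an analysis and an expected result in which age plays no part. Two things are at stake.

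First, the between-group comparisons of the primary outcomes (participation, functional ability, quality of life). With about 13 children per group and an age span of roughly four years, the groups can differ noticeably in mean age by chance. Any part of the change that goes with age is then left as noise, and partly as a chance shift of the group difference.

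Second, the reading of the ALP. The scale grades use of a powered device, and waiting-list children keep their usual routines while the experimental group trains. The gain over the structured program is therefore, by inference, a change within treated children. If development affects how far a young child can progress, the mean gain, and whether it reaches 2 levels, will depend partly on the age mix enrolled.

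**Working it through.** **Inputs from the article.** Ages 10 months to 5 years; 13 evaluable per group; alpha 0.05; effect size 0.5 (Section 2.1). ALP levels 1 to 8 (Section 2.2). Expected gain of at least 2 levels (Section 3).

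**Assumptions not in the article.** Ages uniform over 10 to 60 months, or 10 to 71 months if eligibility runs to the sixth birthday. The correlation r between age and change is unknown; 0.3 to 0.5 is used, with 0.7 as an extreme. The effect size is read as d in a two-sided two-group comparison.

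**The plan's own figure.** The total of 26 is obtained from the between-groups test of a repeated measures ANOVA with f = 0.5, two measures and an assumed correlation of 0.5 between measures. The article does not state that test, metric or correlation. A two-sided two-sample t-test with d = 0.5 would need 64 per group. Here 13 per group is only an input, and the 2-level ALP gain has no derivation to reproduce.

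**Step 1: chance imbalance in age.**
- SD of age = 50/√12 = 14.4 months.
- SE of the difference in means = 14.4 × √(2/13) = 5.7 months.
- 95% range = ±1.96 × 5.7 = about ±11 months.
- Chance of a gap above 6 months, two-sided normal at 6/5.66 = 1.06: 0.29.
- With 10 to 71 months: SD 17.6, SE 6.9, range about ±14 months, chance 0.39.

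**Step 2: what that imbalance could do.** A one-SE imbalance shifts the group difference by r × √(2/13) SD of the change. This is 0.3 × 0.392 = 0.12 SD and 0.5 × 0.392 = 0.20 SD, against a planned effect of 0.5.

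**Step 3: what adjustment buys.** The residual variance falls to 1 − r², so the standardised effect becomes 0.5/√(1 − r²). The noncentrality is that value times √(13/2), with 23 degrees of freedom instead of 24 (critical t 2.069 instead of 2.064).

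| r | variance removed | power, 13 per group |
|---|---|---|
| 0 | 0% | 0.23 |
| 0.3 | 9% | 0.25 |
| 0.5 | 25% | 0.29 |
| 0.7 | 49% | 0.40 |

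At r = 0 the loss is negligible: power is 0.23 with or without the covariate.

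**Step 4: the ALP statements side by side.** The limitation concerns the *level reached*, while the expectation concerns a *gain* of 2. On a scale of 1 to 8, any child starting at level 8 − 2 = 6 or below has room for that gain, and a move from 1 to 3 meets it without reaching a high level. Both statements can be true. However, entry is restricted to children with little or no powered-mobility experience. If most therefore start near the bottom (an inference, since no baseline ALP is given), level reached and gain become nearly the same quantity. A developmental limit on one would then bear on the other.

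**The case against.** The strongest objection is that Section 2.8 is a short statistical section in a journal article. Covariates are commonly left to the full protocol or analysis plan, neither of which is shown. A reader might infer that no analysis of this trial uses age. The article does not support that, and the missing covariate alone would be no finding. What stands is narrower: the article raises the age issue, commits to named tests without an age term, and states one expectation for all ages.

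Other parts of the objection hold and limit the point:

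- A reader might take the Discussion to say that age limits scores in general. It is hedged, and it speaks of the ALP only. The article says nothing of the kind about its primary outcomes, so the case for adjusting those is an ordinary precision argument.
- A reader might see a contradiction between Sections 3 and 4. Step 4 shows there is none. The 2-level figure is also a narrative expectation for a secondary outcome; it is not a test, a success criterion or a sample-size input.
- The imbalance figures in Steps 1 and 2 concern comparisons between groups and do not bear on a within-child ALP gain.
- Within-child contrasts in repeated measures ANOVA already remove stable differences between children, including age-related differences in level. Only age-related differences in *change* over a few weeks remain, and their size is unknown. At r = 0.2 adjustment would remove only 4% of the variance.
- Because the Introduction says "providing independent mobility should occur around between 7 and 12 months", a reader might fault the article for calling the intervention early when entry runs to 5 years. The Introduction puts this as an ideal and does not say that benefit ends there, and the enrolled range is stated openly. That is a preference about wording.

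**Conclusion.** The point holds as a worthwhile improvement to the stated analysis. No figure in the article is shown to be wrong, and the group comparison is not biased, because randomisation prevents systematic age differences. What remains is chance imbalance (SE 5.7 to 6.9 months; a gap above 6 months in 29% to 39% of randomisations, under uniform ages) and age-related change left in the error term.

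The benefit of adjusting is modest: power goes from 0.23 to between 0.25 and 0.29 for r = 0.3 to 0.5. These powers depend on reading 0.5 as d in a two-group comparison. They show the relative gain from adjustment and are not a finding on the sample size. For the ALP, the expected gain needs to be read together with the limitation the article already concedes.

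**What to change.** In Section 2.8, prespecify age at entry, in months and continuous, as a covariate in the between-group models for YC-PEM, PEDI-CAT and PedsQL. In a repeated measures model, age should be allowed to act on change as well as on level. If this is already set out in the full protocol or analysis plan, a pointer to it is enough.

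For the ALP, state that the gain will be reported in relation to age, for example plotted or regressed on age across the whole range, and place the 2-level expectation in Section 3 beside the limitation in Section 4. Estimates at single ages should not be promised. With 13 children and uniform ages, a straight-line estimate at 12 months has leverage 1/13 + 23²/(12 × 14.43²) = 0.29 and a 95% half-width of 2.20 × √0.29, about 1.2 residual SDs, which is too wide to be useful.

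The cost is wording, plus one degree of freedom for a comparison of change (24 to 23). Age is known already, because it is an eligibility criterion. The choice should be fixed before outcome data are seen.
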